#### Missing binary or categorical outcome data

No formal imputation techniques will be used. However, for the primary outcome measure, the following approach will be followed. The element expected to have the highest amount of missing data is wound infection (identified via asepsis scoring [13,14]) measured in hospital and at 3-months follow-up. If in-hospital asepsis scores are missing and the following are true, the patient will be assumed to have no wound infection: (a) no antibiotics for suspected wound infection were prescribed in hospital, (b) follow-up is complete and the patient reported no problems with the healing of the wound at follow-up. Once this has been implemented, if the level of missing data is greater than 5%, this is likely to be mainly due to missing follow-up data and therefore separate treatment estimates will be made for the primary outcome: (a) at hospital discharge, and (b) at any time.

### Subgroup analyses

Seven pre-specified subgroup analyses of the primary outcome are stated in the study protocol: (a) operation type (isolated coronary artery bypass graft versus other operation types), (b) age at operation (<75 years versus ≥75 years), (c) preoperative diagnosis of diabetes (none versus diet, oral medication or insulin controlled), (d) preoperative diagnosis of lung disease (none versus chronic pulmonary disease or asthma), (e) preoperative renal impairment (estimated glomerular filtration rate ≤60 ml/min versus >60 ml/min), (f) sex (men versus women), (g) preoperative ventricular function (good (>50%) versus moderate or poor (≤50%)).

Each subgroup analysis will be performed by adding a relevant interaction term to the primary outcome logistic regression model (for example, for sex, a sex*treatment interaction term will be added to the model) [15]. The hypothesis for all subgroup analyses is that there will be no interaction. Odds ratios and 95% confidence intervals within each subgroup will be given alongside *P* values from the results of tests for interactions. *P* values for treatment estimates within each subgroup will not be given, unless a statistically significant interaction is found at the 5% level.

### Sensitivity analyses

The following sensitivity analyses have been identified; these were not pre-specified in the study protocol:Examining treatment estimates for the primary outcome by site, ordering sites by rates of severe non-adherence with the transfusion protocol: the hypothesis is that the treatment effect should tend towards the null with increasing non-adherence.Assessing the effect of the timing of primary outcome following randomization on the primary outcome by excluding all events that occurred in the first 24 hours after randomization: the hypothesis is that events in the first 24 hours are unlikely to be due to a post-randomization transfusion.Assessing the effect of the transfusions before randomization on the primary outcome by excluding patients who were transfused prior to randomization.Assessing the effect of acute kidney injury: acute kidney injury is defined according to the Acute Kidney Injury Network criteria [16] as either: (a) an increase in serum creatinine concentration (≥26.5 μmol/l, or ≥150% change from baseline) over a period of less than 48 hours, (b) restricted urine output (<0.5 ml/(kg h)) for more than 6 hours or (c) the need for renal replacement therapy. Highest daily creatinine levels are recorded separately from clinical judgment of acute kidney injury, so the following sensitivity analyses are planned to re-analyze the primary outcome: (a) excluding patients identified with acute kidney injury who do not have an increase in serum creatinine concentration over a 48 hour period or less, according to the daily highest creatinine concentration values collected, (b) including patients who have not been identified as having acute kidney injury, but according to the daily highest creatinine concentration data have a rise in serum creatinine concentration that would meet the criteria (and who were not having haemofiltration or dialysis pre-operatively).Serious primary outcome events: the pre-planned interim analysis after half the study participants had been recruited showed that the majority of the primary outcome events are either sepsis or acute kidney injury, and therefore the primary outcome will be re-analyzed including only the more ‘serious’ events. This will mean the following changes to the definition of the overall primary outcome: (a) all myocardial infarctions, gut infarctions and strokes will be included, (b) only the most severe acute kidney injury cases (stage 3) will be included, (c) all wound infections identified via asepsis scoring will be excluded (the more serious wound infections will be identified via serious sepsis events), (d) serious pre-discharge sepsis events will be identified by the presence of sepsis plus organ failure (defined as: myocardial infarction, stroke, acute kidney injury, laparotomy for gut infarction and one or more of reintubation, acute respiratory distress syndrome, low cardiac output or tracheostomy), (e) post-discharge sepsis events will be included, as they require hospitalization.

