### Adherence to the study protocol

Assumptions regarding transfusion rates in the two groups were made in calculating the sample size [7]; if transfusion rates do not match these assumptions, the power of the study will be reduced. Therefore, measuring and assessing adherence with the transfusion protocol is critical. Non-adherence is defined in two ways: (a) the patient received a RBC transfusion outside of the protocol (‘extra’ transfusion) and (b) the patient was not given a RBC transfusion that, according to the protocol, should have been given (‘withheld’ transfusion). Adherence will be assessed for the period from randomization to hospital discharge, although if a patient withdraws or has treatment discontinued, adherence after the time of withdrawal or discontinuation will not be assessed. For both types of non-adherence, instances will be classified as mild, moderate or severe (see Table 1), according to the likely influence on transfusion rates, and therefore possible influence on study outcomes.

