**Table 1 Tab1:** **Non-adherence to transfusion protocol**

	**Transfusion outside of protocol**	**Transfusion according to protocol withheld**
Mild	Not applicable	A transfusion took place, but more than 24 hours after the breach of the relevant transfusion threshold
Moderate	Patient transfused, but patient did breach the relevant threshold for transfusion at some point postoperatively (before or after the transfusion outside of protocol)	Patient was not transfused following a breach, but the patient had previously had at least one post-randomization transfusion
Severe	Patient transfused, and patient did not breach the relevant threshold for transfusion at any point postoperatively	Patient was not transfused following a breach, and patient had no post-randomization transfusions

A patient can breach the relevant threshold for transfusion several times, and so there can be more than one case of non-adherence per patient.

The frequency of each type of non-adherence will be described by treatment allocation. Further descriptive analyses will be undertaken, to look at non-adherence in more detail, including: reasons for non-adherence, number of deviations from the protocol per patient, haemoglobin or haematocrit levels at deviations and the day of the week and time of the day of deviations. Characteristics of patients with or without any non-adherence will be compared and non-adherence rates will be described by site.

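### Ordering sites by a single rate of severe non-adherence counts one deviation that widens the exposure contrast together with two that narrow it, so sites can be misordered for dilution

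*SAP article*

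**What the plan says.** Under *Sensitivity analyses*, the first item examines site-level estimates of the primary treatment effect, "ordering sites by rates of severe non-adherence with the transfusion protocol", and adds that "the hypothesis is that the treatment effect should tend towards the null with increasing non-adherence". It mentions no split by arm or by type of deviation.

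The grade comes from *Adherence to the study protocol* and Table 1. "Non-adherence is defined in two ways": extra transfusions and withheld ones. Each is graded "according to the likely influence on transfusion rates, and therefore possible influence on study outcomes". Table 1 gives the severe grade to an extra transfusion when "Patient transfused, and patient did not breach the relevant threshold for transfusion at any point postoperatively", and to a withheld one when "Patient was not transfused following a breach, and patient had no post-randomization transfusions". Both definitions refer to the threshold of the patient's own arm, so the grade does not depend on allocation.

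Two descriptive summaries are also planned: "The frequency of each type of non-adherence will be described by treatment allocation", and "non-adherence rates will be described by site". Neither is carried into the ordering of sites.

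**The concern.** The severity grade measures how much a deviation is likely to alter transfusion rates, not in which direction. The hypothesis attached to the ordering is about direction: more non-adherence should mean a more diluted effect. That fits deviations that bring the two arms' exposure closer together, but not one that moves them further apart.

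At stake is how a secondary display is read. The section on adherence treats adherence as critical because departures from the assumed transfusion rates cost power. This is the only item in the list of sensitivity analyses that relates non-adherence to the primary treatment estimate. If the sort variable mixes directions, a flat or irregular pattern could be taken as a sign that non-adherence did not dilute the result, although the sites were not strictly ordered by dilution.

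**Working it through.** **Which severe deviations can occur.** *Flow of participants* makes a haemoglobin below 9 g/dl or haematocrit below 27% the condition for randomization. *Methods and Design* uses the same values as the liberal threshold. Every eligible liberal patient has therefore breached, and a severe extra transfusion cannot arise in that arm. Three kinds remain:

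| Severe deviation | Effect on exposure contrast |
|---|---|
| Extra, restrictive arm | narrows |
| Withheld, liberal arm | narrows |
| Withheld, restrictive arm | widens |

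**Formula.** The plan gives no figure on this point, so what follows is an illustration. Let b be the share of restrictive patients who breach their threshold (assumed; not in the document). Let S be the site's severe rate over both arms, with equal arms and one severe deviation per affected patient. Let f be the share of severe cases that are restrictive-withheld. The contrast is the proportion given any post-randomization transfusion, liberal minus restrictive:

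contrast = (1 − b) − 2S(1 − f) + 2Sf = (1 − b) − 2S(1 − 2f)

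Each point of S removes 2 points of contrast if it is of a narrowing kind and adds 2 points if it is restrictive-withheld. The net effect is zero at f = 1/2, whatever b is.

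**Single-kind limits at S = 10%.** These are extremes and show direction only.

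| b | No severe cases | All narrowing (f = 0) | All restrictive-withheld (f = 1) |
|---|---|---|---|
| 0.20 | 80 points | 60 | 100 |
| 0.35 | 65 points | 45 | 85 |
| 0.50 | 50 points | 30 | 70 |

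**Misordering, b = 0.35.**
- Site A, S = 4%, f = 0: 0.65 − 0.08 × 1 = 0.57.
- Site B, S = 8%, f = 0.75: 0.65 − 0.16 × (1 − 1.5) = 0.73.
- Site C, S = 8%, f = 0.50: 0.65 − 0.16 × 0 = 0.65.
- Site D, S = 8%, f = 0.25: 0.65 − 0.16 × 0.5 = 0.57.

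The plan's ordering puts B, C and D beyond A for non-adherence. By contrast, B and C are less diluted than A, and D is equal to it. A site is misordered when S(1 − 2f) and S rank differently, so a share that varies between sites is enough; it need not exceed one half.

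**How large the share might be.** If every patient at risk had the same chance of a severe deviation, then per 100 patients per arm there are 100 liberal patients and 100(1 − b) restrictive non-breachers at risk of a narrowing deviation, and 100b restrictive breachers at risk of a widening one. Hence f = b/2:
- b = 0.30: 15% widening, 85% narrowing.
- b = 0.40: 20% and 80%.
- b = 0.60: 30% and 70%.

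Reaching f = 1/2 needs a rate among restrictive breachers of (2 − b)/b times the rate elsewhere: 5.7, 4.0 and 2.3 times respectively.

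**Precision of the display.** With 2,000 patients in 17 centres of equal size (assumed), a site has 2,000/17 ≈ 118 patients, about 59 per arm. At the planned 17% and 11%, the odds ratio is (0.11/0.89)/(0.17/0.83) = 0.60. The standard error of its logarithm is √(1/10.0 + 1/48.8 + 1/6.5 + 1/52.4) ≈ 0.54, giving a 95% interval of about 0.21 to 1.75.

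**The case against.** A reader might infer that the trend to the null does not follow from this ranking at all. The document does not support that. Most patients at risk of a severe deviation are at risk of a narrowing kind, and at equal rates 70% to 85% of severe cases dilute (b from 0.60 to 0.30). If the restrictive-withheld share is well under one half and similar across sites, the plan's ordering still points the right way on average. The misordering example also needs a strong assumption: site B has 12% of its restrictive patients severe-withheld, about a third of its breachers (0.12/0.35). Nothing in the document says this happens.

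A reader might also infer that withholding in the restrictive arm enlarges the treatment effect. That step assumes risk is monotone in transfusion. The primary outcome includes ischaemic events, and the trial exists because a safe restrictive threshold is uncertain, so the document does not settle the direction on the outcome. Only the direction on exposure is established. This is itself a reason to keep the kinds apart.

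Three further points stand. Description by allocation will show at trial level whether restrictive-withheld cases are common, though not site by site within arm. The ancillary instrumental-variable work also uses transfusion actually received, so this item is not the only place where exposure meets outcome. Finally, the item sets no test or decision rule, and the site estimates are so imprecise that a trend would be hard to see under any ordering.

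**Conclusion.** The point holds in a limited form. The sort variable does not fully match the hypothesis attached to it, because one of the three possible severe deviations works against dilution of exposure, and no other part of the document corrects this. The direction follows from the plan's own definitions and holds for every breach proportion tried. The size cannot be determined: it depends on the restrictive-withheld share of severe cases and on how much that share varies between sites, and neither is given. The illustration rests on an assumed breach proportion, equal arms within site and one severe deviation per affected patient.

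The priority is minor. This is a secondary, descriptive and imprecise analysis, and the primary estimate is untouched.

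**What to change.** Order sites by contrast-reducing severe non-adherence only: severe extra in the restrictive arm plus severe withheld in the liberal arm. Attach the hypothesis of a trend to the null to that ordering alone. Tabulate severe withheld cases in the restrictive arm by site separately, claiming no direction for their effect on the outcome. Add a sentence that a flat pattern across sites is not to be read as absence of dilution, given the width of the site-level intervals.

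Do not order sites by the achieved between-arm difference in transfusion. Under perfect adherence that difference is 1 − b, so it would be 70 points at a site where 30% of restrictive patients breach and 40 points where 60% do. It would mix each site's breach proportion with its adherence.

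The cost is a change of wording and of sort variable, because type and allocation are already recorded. The downside is fewer deviations per site in the ranking, and the site estimates stay as imprecise as before. The *Discussion* says the plan has already been executed, so the re-ordered display would be reported alongside the planned one and labelled post hoc.

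### AKI sensitivity analysis (a) is worded to drop patients on a post-randomization outcome, and its creatinine rule does not match the plan's own three-route AKI definition

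*SAP article*

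**What the plan says.** Everything at issue is in the SAP article, under Sensitivity analyses.

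**Definition of AKI.** Any one of three routes is enough. The first is "an increase in serum creatinine concentration (≥26.5 μmol/l, or ≥150% change from baseline) over a period of less than 48 hours". The second is "restricted urine output" below a stated rate, and the text continues "for more than 6 hours or (c) the need for renal replacement therapy".

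**Reason for the AKI re-analyses.** "Highest daily creatinine levels are recorded separately from clinical judgment of acute kidney injury", so the primary outcome is to be re-analyzed in two ways.
- Analysis (a) works by "excluding patients identified with acute kidney injury who do not have an increase in serum creatinine concentration over a 48 hour period or less", judged on the daily highest creatinine values.
- Analysis (b) brings in patients not identified with AKI whose recorded creatinine rise would meet the criteria, "and who were not having haemofiltration or dialysis pre-operatively".

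**Serious-events re-analysis.** Under its item (b), "only the most severe acute kidney injury cases (stage 3) will be included". Under its item (d), "serious pre-discharge sepsis events will be identified by the presence of sepsis plus organ failure (defined as: myocardial infarction, stroke, acute kidney injury", followed by laparotomy for gut infarction. The phrase 'and one or more of' then introduces four respiratory and cardiac items.

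The plan states that none of these sensitivity analyses was in the protocol.

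**The concern.** Analysis (a) asks whether the primary result depends on clinically judged AKI that the recorded creatinine does not support. That is a sensible question in an open trial. The wording answers a different one in three respects.

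- It speaks of patients, not of the AKI component. Removing people because of something that happened after randomization breaks the randomized comparison, and it also loses any other true event those people had.
- It tests creatinine alone, although the definition accepts two other routes. A case that is valid by urine output or renal replacement would be removed together with the unsupported ones.
- It does not say how large a rise counts, and its window is not that of the definition.

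The serious-events re-analysis has a smaller problem of the same kind, because two readers could derive different event sets from it. It was prompted by the interim analysis, which found that most primary events were sepsis or AKI, so its derivation should leave no discretion.

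**Working it through.** **Step 1: the AKI rules side by side.**

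| Feature | Definition | Analysis (a) | Analysis (b) |
|---|---|---|---|
| Routes | Creatinine, urine output or renal replacement | Creatinine only | Creatinine only |
| Size of rise | Stated | Not stated | Must meet the criteria |
| Window | Less than 48 hours | 48 hours or less | By reference to the criteria |
| Renal replacement | Qualifies | No exemption | Pre-operative treatment bars inclusion |

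A patient who started renal replacement after surgery without a recorded creatinine rise is a valid case in the first column and is removed in the second.

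**Step 2: patients or events.** The same section speaks of excluding events in the first 24 hours when it means events, and of excluding patients transfused before randomization when it means people. Analysis (a) uses the second form. Analysis (b), however, includes patients who are already in the analysis population, so there the verb can only mean counting them as events. The text supports either reading of (a).

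**Step 3: what the two readings do (illustration only).** The document does not say how many events are AKI without a creatinine rise. Inputs from Sample size: 17% and 11%, total 2,000, 1:1, hence 170 and 110 events per 1,000. As background, the stated 1,468 is reproduced: two proportions, 90% power, two-sided 5%, with continuity correction, give 734 per arm and 2 × 734 = 1,468.

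Assume a share f of events, equal in both arms, is affected, and that these patients had no other component event.

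- Kept as non-events: OR = [110(1−f)/(1000−110(1−f))] ÷ [170(1−f)/(1000−170(1−f))].
- Dropped: the non-events stay at 890 and 830, so OR = [110(1−f)/890] ÷ [170(1−f)/830] = (110/890)/(170/830) = 0.603 for every f.

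| f | Events affected (of 280) | Kept as non-events: OR, power | Dropped: OR, power |
|---|---|---|---|
| 0 | 0 | 0.603, 97.2% | 0.603, 97.2% |
| 10% | 28 | 0.608, 95.4% | 0.603, 95.9% |
| 20% | 56 | 0.613, 92.6% | 0.603, 94.0% |
| 30% | 84 | 0.618, 88.5% | 0.603, 91.1% |
| 50% | 140 | 0.627, 74.9% | 0.603, 80.9% |

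Power here uses the normal approximation without continuity correction.

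The constant 0.603 comes from the equal-share assumption. With shares fL (liberal) and fR (restrictive), the dropped OR is 0.6034 × (1−fR)/(1−fL).
- fL = 10%, fR = 20%: dropped 0.6034 × 0.8/0.9 = 0.536; kept (88/912)/(153/847) = 0.534.
- fL = 20%, fR = 10%: dropped 0.6034 × 0.9/0.8 = 0.679; kept (99/901)/(136/864) = 0.698.

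**Step 4: other events lost by dropping.** If 20 patients per arm were removed and a share g had another component, 20 × g true events per arm disappear: 2 at 10%, 6 at 30%, 10 at 50%. All these inputs are assumed.

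**Step 5: the serious-events items.** If the organ-failure list is one of alternatives, myocardial infarction, stroke and gut infarction already count under item (a), and stage 3 AKI under item (b). Item (d) then adds only sepsis with AKI below stage 3, or sepsis with one of the four respiratory and cardiac items. If the joining words are a true conjunction, AKI alone does not make sepsis serious. The two readings give different event sets.

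**The case against.** The strongest defence is that a sensitivity analysis may use a narrower definition on purpose. The plan gives its reason, and (a) and (b) form a pair: one takes away judged AKI that creatinine does not support, the other adds creatinine-supported AKI that was not judged. This stands. A creatinine-only check is legitimate, and a reader who infers that (a) is invalid merely for being narrower than the definition goes too far. What remains is that (a) is not labelled as creatinine-only and is silent on the other two routes.

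The parallel with (b) also suggests that the AKI, not the patient, was to be set aside. This shows ambiguity but does not settle it, because the same section uses the wording of (a) elsewhere to mean removing people.

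A further objection is that sparing every urine-output and renal-replacement case would bring (a) close to the main definition and blunt the check. This has force, and reporting such cases separately meets it.

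For the serious-events re-analysis, a reader might infer that mild AKI re-enters in breach of the AKI definition, so that the analysis fails in its purpose. The text does not support that. The tension is with the stage 3 limit in item (b). Item (d) counts a different event, sepsis with organ failure; AKI below stage 3 without sepsis stays out, as do pre-discharge sepsis without organ failure and wound infections found only by asepsis scoring. Accepting any stage of AKI as organ failure in sepsis is a choice of definition. The re-entry and conjunction complaints also depend on opposite readings of the list, so they cannot both hold.

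**Conclusion.** The point holds for analysis (a). Taken literally, it drops patients on a post-randomization outcome, loses their other true events, and removes cases that are valid under the plan's own definition, with no stated size of rise and a window that differs from the definition. For the serious-events re-analysis, what holds is narrower: items (b) and (d) treat AKI severity differently, and the organ-failure list can be read in two ways.

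The size cannot be determined from the document. In the illustration with equal shares of 10% to 50%, the cost is mainly power, and the odds ratio moves little or not at all. With unequal shares it moves more, but the gap between dropping and recoding stays small (0.679 against 0.698 at most in the cases shown). Those comparisons assume that the affected patients had no other component event, so the events in step 4 would be a further loss.

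A reader might infer that the trial's main result is compromised. It is not: the primary analysis keeps the full definition and every patient in its population. The consequence is confined to how far these sensitivity analyses can be relied on.

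**What to change.** **Analysis (a).** Keep every patient in the analysis population, recode only the AKI component as absent, and recompute the composite, so that a patient with another component event remains an event. Label it as a creatinine-confirmed check. Use the definition's creatinine threshold and window, and say how the window is applied to daily values. Do not treat documented renal-replacement cases, or urine-output cases where these were recorded, as unconfirmed; alternatively, report them separately.

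**Serious-events re-analysis.** Reconcile items (b) and (d) on the stage of AKI, and state whether any one listed organ failure is enough. Which stage should apply is for the investigators to decide.

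**Cost.** A few sentences and a little derivation code. The limit is which AKI criteria were recorded for each patient; this section mentions separate recording only for creatinine. Because the Discussion says the plan has since been executed, the practical step is to state which derivation was used and to rerun these analyses if it was the literal one.
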